Transvaginal sealing of cervical cancer ensures that the whole laparoscopic radical hysterectomy(LRH)operation is completed without tumor exposure. After satisfactory anesthesia, the patient took the bladder lithotomy position, performed routine disinfection, sewed the anal protective towel in the perineal water to prevent pollution, and fixed the bilateral labia minora. After vaginal disinfection again, the upper and lower vaginal hooks exposed the vagina and cancerous cervix, and the length of the vagina to be removed was determined according to the scope of lesions (usually ≥ 3 cm). Six tissue forceps were used to clamp the four walls of the vagina at the lower edge of the vaginal wall to be removed, Inject a water pad (1 mg adrenaline diluted with 500 mL normal saline) under the mucosa of the intended vaginal excision with a syringe to facilitate the separation of the vaginal wall from the bladder and rectum and reduce bleeding. Cut the vaginal wall in a circular way along the clamp of the tissue forceps with a unipolar electric knife and slightly mechanically separate it. Suture the nodules on the front and rear walls of the initially separated lower edge of the vagina to seal the cervical cancer. While pulling the suture downward, pull the hook upwards to pull the bladder and rectum, adhere to the vaginal wall along the bladder vaginal gap and rectum vaginal gap, and use sharp scissors combined with blunt fingers to further separate the vaginal wall to be removed until the bladder and rectum are folded peritoneum. At the same time, further expand the separation to both sides, reaching the knees of both ureters in the front and the bilateral uterosacral ligaments in the back. The adjacent vaginal tissues on both sides are cut off by external forceps, Suture the broken end. In order to ensure the principle of tumor free to the greatest extent, rinse the vagina with saline again and collect the washing solution for tumor cytology. After the second iodophor disinfection, the front and back of the vagina are filled with gauze to reach the front and back of the retroflex peritoneum, and then start the laparoscopy. The fundus sutures were pulled instead of lifting the uterus. The absorbable line No. 1 was used to perform Fig. 8 sutures on the fundus. The intraoperative assistant clamps the suture line to swing the uterus to avoid the use of lifting the uterus.

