### Criteria for discontinuation of trial treatment

The criteria for the discontinuation of a trial medication are as follows:A participant declines further participation or withdraws their consent.Cancelation of the entire study.Death.The protocol treatment will be stopped if the annual patient accrual is less than 30, less than 75% of patients are available for follow-up, or an unacceptable rate of the incidence of complications (8%) occurs in the gasless TLRH group.Severe adverse events (progressive or persistent) which may be related to the surgery (such as severe surgical complications, fistula, for example, occur more than 3%) and newly diagnosed other malignancies (e.g., breast cancer, excluded transfer) will be evaluated by 2 chief physicians before the trial is stopped.Any situation in which the treatment cannot be continued according to the judgment of the physician [19].

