### Discontinuation of the study

The study will be terminated early if the IRB determines the occurrence of any of the following: serious surgical complications (fistula); the participants with unexpected, significant, or unacceptable risks (such as death); the trial treatment is determined to be ineffective [19].

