#### Secondary outcome measures (compare between arms)

Operation time: The time from the start of the operation to the end of the operation.

Length of stay: The time from admission to discharge.

Estimated blood loss. Blood loss will be defined as the total volume of suctioned fluids minus the volumes of irrigation fluids used at the completion of surgery.

The levels of CD4^+^ T lymphocytes, NK cells, and CD4^+^ CD25^high^ CD127^low^ Treg in peripheral blood before and after operation; postoperative peritoneal immune factors IL-6, TNF-β, and TNF-α levels.

Hemodynamic parameters (cardiac output before and at the end of surgery, CO), mean arterial pressure (MAP), and stroke output (stroke volume (SV)). Pco2, blood gas analysis, ion profile.

Intraoperative complications (injury to bladder, ureters, bowel, blood vessels and bleeding, and nerves).

Perioperative complications: urinary tract infection, urinary retention, ileus, myocardial infarction, atrial fibrillation, pulmonary edema, atelectasis, pneumonia, renal and cerebrovascular morbidity, and thromboembolic complications (deep vein thrombosis, pulmonary embolism).

Early (4 weeks) postoperative complications: pulmonary, renal, and cerebrovascular morbidity; wound and vault complications (infection, breakdown, and dehiscence); septicemia and thromboembolic complications (deep vein thrombosis, pulmonary embolism); and lymphocyst or abscess formation.

Delayed postoperative complications (4 weeks–6 months after surgery): lymphedema, incisional hernia formation, vaginal evisceration.

Postoperative pain and analgesic consumption using pain scores and analgesic consumption measurements.

Costs: measured as the incremental cost/unit of improvement in functional outcome, measured in terms of the primary outcome plus using quality-adjusted life years to undertake a cost-use analysis.

The quality of life instruments(QOL) (FACT-Cx, SF12, EQ-5D, MDASI): change in QOL using functional assessment of cancer therapy-cervical between baseline (presurgery) and 6 months after surgery.

Pelvic floor distress inventory: measures symptom severity and QOL changes in women with pelvic floor disorders. The pelvic floor distress inventory provides a standardized, reproducible assessment of the patient’s symptoms and their effect on daily life.

The OS at 4.5 years follow-up [8].

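### The between-arm complication outcomes have no entry for fistula, which the protocol names as a ground for stopping, and several early complications fit no outcome after week 4

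*Protocol article*

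**What the plan says.** In the Protocol article, the section Secondary outcome measures (compare between arms) gives complications as four lists.

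- Intraoperative: "Intraoperative complications (injury to bladder, ureters, bowel, blood vessels and bleeding, and nerves".
- Perioperative, with no time window: "Perioperative complications: urinary tract infection, urinary retention, ileus, myocardial infarction, atrial fibrillation, pulmonary edema, atelectasis, pneumonia, renal and cerebrovascular morbidity", followed by thromboembolic events.
- Early (4 weeks): organ morbidity, "wound and vault complications (infection, breakdown, and dehiscence", septicemia, thromboembolic events, and lymphocyst or abscess.
- Delayed: "Delayed postoperative complications (4 weeks–6 months after surgery): lymphedema, incisional hernia formation, vaginal evisceration".

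None of the lists has open-ended wording such as a leading example or a residual category.

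Two other sections name fistula. Criteria for discontinuation of trial treatment refers to severe events related to surgery, "such as severe surgical complications, fistula, for example, occur more than 3" per cent, to be evaluated before the trial is stopped. Discontinuation of the study gives "serious surgical complications (fistula" as a ground for early termination.

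In Table 1 the row for treatment-related morbidity is ticked at 1 week, 6 weeks, 3 months and 6 months, and is blank for later follow-up. The Abstract names treatment-related morbidity first among the secondary aims.

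**The concern.** The event that the protocol treats as serious enough to stop the trial is not among the events that it plans to compare. A reader of the final report would look to the complication outcomes for the morbidity comparison and find no line for fistula. If fistulas were then tabulated, the definition and the time span would have been chosen after the data were seen.

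The time windows cause a second gap. Several complications count only if they start within 4 weeks, because the delayed list holds three other conditions.

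This matters because the Discussion's case for gasless laparoscopic surgery rests partly on better short-term well-being at equal survival. The prespecified complication comparison is a main test of that.

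The 8% rule, "an unacceptable rate of the incidence of complications (8%) occurs in the gasless TLRH group", does not define complications. If the outcome lists were taken as its definition, fistula would fall outside that rule too.

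**Working it through.** The protocol gives no figure to reproduce here. The check is a comparison of sections plus simple arithmetic for scale.

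**Step 1. The four lists side by side.**

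| Outcome list | Stated window | Fistula listed | Vault infection or breakdown, septicemia, lymphocyst, abscess listed |
|---|---|---|---|
| Intraoperative | the operation | no | no |
| Perioperative | none stated | no | no |
| Early | 4 weeks | no | yes |
| Delayed | 4 weeks to 6 months | no | no |

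A lymphocyst or vault infection that starts in week 5 is too late for the early list and is not named in the delayed list. Thromboembolic, renal and cerebrovascular events are weaker examples. They also appear in the perioperative list, whose end is not stated. Vault dehiscence is partly covered later through vaginal evisceration.

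**Step 2. How much of the assessment period is affected.** Treatment-related morbidity is scheduled over 6 months, about 26 weeks. The delayed window takes 26 − 4 = 22 of these, or 22/26 = 85%. Three of the four scheduled morbidity assessments (6 weeks, 3 months, 6 months) fall in it. These are shares of time and visits, not of events.

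**Step 3. Scale of the fistula gap.** Inputs are 370 patients per arm (Sample size) and the 3% level (Criteria for discontinuation of trial treatment).

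- One arm: 0.03 × 370 = 11.1. A rate above 3% at full enrolment needs 12 fistulas (12/370 = 3.2%; 11/370 = 3.0%, just under).
- Both arms pooled: 0.03 × 740 = 22.2, so 23 fistulas. Both are shown because the criterion names no arm.

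In either case the listed outcomes contain no entry for these events.

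**Step 4. What a listed fistula outcome could show.** The documents give no fistula rates, so the rates below are assumptions. With n = 370 per arm, p̄ the mean of the two rates and a two-sided 5% test, power = Φ{[(p₂ − p₁) − 1.96·√(2p̄(1−p̄)/n)] / √[(p₁(1−p₁) + p₂(1−p₂))/n]}.

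- 1% against 3%: (0.0200 − 0.0202)/0.0103 = −0.02, power 49%.
- 1% against 5%: (0.0400 − 0.0246)/0.0125 = 1.24, power 89%.

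Only a large difference would be detected reliably. The value of listing fistula lies in a prespecified estimate with its 95% confidence interval, more than in a test.

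**Step 5. What is recorded elsewhere.** Treatment of adverse events has each adverse event described in a case report form, with nature, onset, severity and outcome, and sets neither an event list nor an end date. Phase II analysis plans descriptive statistics on treatment-related adverse events and an as-treated toxicity analysis. Table 1 continues concomitant illnesses, physical examination and CT of the pelvis and abdomen through follow-up.

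**The case against.** The strongest reply is that nothing is lost. Every adverse event goes into a case report form, treatment-related events are summarised, discrete variables are compared by chi-squared test, and the data monitoring committee sees all trial data. The lists are not declared exhaustive, and a journal article may leave coding rules to the full protocol. A 6-month horizon for surgical morbidity is also a legitimate choice.

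Much of this stands. A reader might infer that fistulas and late complications would vanish from the trial's safety data, but the adverse-event provisions rule that out. The 6-month limit is not in itself an error.

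The reply does not remove the mismatch. The article does not leave the matter open: it states the lists and the windows, and they do not match its own stopping sections. General adverse-event reporting with descriptive summaries is not a defined between-arm outcome, particularly in an open-label trial. Some fistulas might be coded as a vault breakdown or traced to an organ injury at operation, but no list says so, and the first route closes at 4 weeks.

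A reader might also infer that fistula is the main harm of the gasless arm and that leaving it out favours that arm. That arm does add a transvaginal step ("use sharp scissors combined with blunt fingers to further separate the vaginal wall to be removed until the bladder and rectum are folded peritoneum") which the account of the abdominal operation does not describe. But neither fistula criterion names an arm, and nothing in the article says that fistula is more frequent in one. Ending the count of incisional hernia at 6 months could work in the opposite direction, since the abdominal arm has a midline incision. No direction of bias can be claimed.

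**Conclusion.** The point holds as a defect in the prespecified complication outcomes. None of the four lists includes fistula, although two sections make it a ground for stopping. At least four kinds of complication (vault infection or breakdown, septicemia, lymphocyst, abscess) have no outcome once week 4 has passed. At the protocol's own 3% level, about 11 of 370 patients in one arm would have an event with no place in the listed comparison. This is an illustration at a stopping level, not a forecast.

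The conclusion assumes that the lists are applied as written. It does not extend to the primary endpoint or to adverse-event reporting in general. Nor do the documents show how many hernias or cases of lymphedema would arise after 6 months. The counted period is 6 of 54 months (11%), but that is a share of time and says nothing about the share of events. The point should be corrected, at little cost.

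**What to change.** In Secondary outcome measures:

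1. Add urinary and bowel fistula as a complication outcome.
2. Use one common event list for the early and delayed windows. Record the onset date of each event and count it in the window where it falls.

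In Criteria for discontinuation of trial treatment and Discontinuation of the study, use the same fistula definition and count as in the outcome, so that the sections agree. Their thresholds stay as they are.

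Optionally, record fistula, hernia and lymphedema at the visits already scheduled after 6 months, extend the Table 1 row for treatment-related morbidity accordingly, and report them by arm.

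The cost is a change of wording in the protocol and case report form and a little extra data entry. No new visits or procedures are needed.

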**Conclusions:**

This prospective trial aims to show the equivalence of the laparoscopic cervical cancer surgery in the open state versus the transabdominal radical hysterectomy approach for patients with early-stage cervical cancer following a 2-phase protocol.

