### Efficacy assessments

#### The primary outcome is the rate of disease-free survival at 4.5 years

To compare disease-free survival amongst patients who undergo laparoscopic cervical cancer surgery based on open surgery versus those who undergo a total abdominal radical hysterectomy (TARH) for early-stage cervical cancer [8].

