### Sample size

The main purpose of this study is to determine whether gasless laparoscopic radical hysterectomy (gasless TLRH) or equivalent to total abdominal hysterectomy (TARH) is effective in terms of disease-free survival at 4.5 years. If the difference in disease-free survival rate does not exceed 7%, then these two surgeries are considered equivalent.

The estimated 4.5-year disease-free survival rate of patients receiving TARH is 90%. The sample size was based on an expected disease-free survival rate of 90% in the open-surgery group at 4.5 years and a noninferiority margin of 7.2 percentage points for minimally invasive surgery, which reflected an acceptable difference in the expected survival rate of at most 8 percentage points. In previous studies involving patients with other types of cancer, a noninferiority margin of 6 to 8 percentage points has been considered to be clinically acceptable.

Based on these data, a total of 740 patients (370 in each group) will be sufficient to declare equivalence in 4.5 years of accrual and 4.5 years of follow-up, with an equivalence margin of 6% or less at 4.5 years [8].

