## Discussion

This trial is expected to provide high-level evidence that laparoscopic radical hysterectomy with a closed cervical cancer body, no lifting of the uterus, and no pneumoperitoneum may be a valid alternative to abdominal surgery with equal DFS and OS and superior short-term well-being for women diagnosed with early-stage cervical cancer.

It is reported that the continuously perfusing and flowing carbon dioxide in the abdominopelvic cavity could lead to the spread of the detached tumor cells [12, 13, 16]. Gasless laparoscopic surgery (GLS) is an effective operation in the treatment of gynecological diseases with few complications [20].

Investigated the usefulness of GLS using a subcutaneous abdominal wall lifting method for endometrial cancer.GLS for endometrial cancer results in less bleeding, shorter hospital stay, and fewer complications than open surgery. Recurrence and survival rates were not significantly different from those of open surgery [21]. Regardless of whether the CO_2_ pneumoperitoneum environment increased tumor cell growth or spread, our gasless laparoscopy was similar to laparotomy, which may be a protective measure. In the space formed by the suspension of the abdominal wall, the abdominal pressure is consistent with atmospheric pressure, which has little influence on the movement of the diaphragm, reduces the inflow of CO_2_ into the blood, and affects the blood gas. Eliminating the effects and risks related to CO_2_ has higher safety and is less likely to cause significant reactions to the respiratory and circulatory systems.

Andreas Kavallaris et al. retrospective 32 patients with stage FIGO (2009) IB cervical cancer underwent laparoscopic radical hysterectomy without the use of any uterine manipulator. This study showed a better tumor prognosis compared to studies using a minimally invasive approach with routine use of uterine manipulators and no vaginal closure of tumors [22]. In 2020, a large-scale cohort observation study SUCCOR showed that MIRH using different techniques (including avoiding uterine manipulators) yielded comparable results to existing techniques [23]. Therefore, compared to open surgery, cancer cell leakage may lead to poorer tumor prognosis.

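### One of the two cost measures divides by the difference in 4.5-year DFS, which the trial plans to be about zero, so that ratio will usually be uninterpretable

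*Protocol article*

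**What the plan says.** The article's list of secondary outcome measures gives two economic measures in one sentence. The first is a cost-effectiveness ratio, "measured as the incremental cost/unit of improvement in functional outcome, measured in terms of the primary outcome". The second follows directly: "plus using quality-adjusted life years to undertake a cost-use analysis", which I read as a cost-utility analysis.

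The denominator of the first is fixed by the heading under Efficacy assessments: "The primary outcome is the rate of disease-free survival at 4.5 years".

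Three places show what the trial expects of that denominator:
- The abstract's conclusion: "This prospective trial aims to show the equivalence of the laparoscopic cervical cancer surgery in the open state".
- Sample size: "If the difference in disease-free survival rate does not exceed 7%, then these two surgeries are considered equivalent". The open arm is put at 90% DFS at 4.5 years, no gain is stated for the laparoscopic arm, and the calculation uses "a noninferiority margin of 7.2 percentage points for minimally invasive surgery".
- Discussion: the new operation "may be a valid alternative to abdominal surgery with equal DFS and OS and superior short-term well-being".

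The Statistical analysis section adds only that treatment-cost results will be analysed by surgical method. It names no alternative to the ratio.

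**The concern.** A cost per unit of improvement is informative when an improvement is expected. Here the design expects none, so the cost difference is divided by a quantity whose planned value is zero and whose estimate is mostly noise. Three things follow:
- The ratio can be very large in either direction because of a handful of events.
- Its sign carries little information. A negative value can mean cheaper and better or dearer and worse.
- A confidence interval for it is usually unbounded.

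The closer the two arms are on the primary endpoint, the less this number means. Costs and cost-effectiveness are a named secondary aim in the abstract, so an uninterpretable figure could end up in the report of that aim.

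**Working it through.** **Inputs from the article.** 370 per arm, 1:1 allocation; DFS at 4.5 years 90% in the open arm; margin 7.2 points; 95% confidence intervals for group differences (Statistical analysis).

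**Assumptions of mine.** DFS of 90% in the laparoscopic arm as well (varied below), binomial variance, and all 370 per arm evaluable at 4.5 years.

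**Step 1: is a zero difference consistent with the stated sample size?** The article gives neither alpha nor power. Taking one-sided 0.025 and 90% power, with 90% DFS in both arms:

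n per arm = 2 × 0.9 × 0.1 × (1.960 + 1.282)² / 0.072² = 364.8, so 365 per arm and 730 in total, within 3% of 740. At 370 per arm the implied power is 90.4%.

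The match is not unique. For example, a 6-point margin, one-sided 0.05 and 85% power gives 720. It shows only that the stated size is consistent with planning for equal DFS.

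**Step 2: precision of the denominator.**

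SE = √(2 × 0.9 × 0.1 / 370) = 0.0221, or 2.2 points. The 95% half-width is 1.96 × 2.2 = 4.3 points.

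**Step 3: sign of the denominator when true DFS is equal.** From two Binomial(370, 0.9) counts:
- positive in about 48% of trials (47.6%);
- negative in about 48% (the same by symmetry);
- exactly zero, so that the ratio is undefined, in 4.9%;
- smaller than 1 point in size in 33% (35% by normal approximation).

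**Step 4: spread of the ratio.** Hold the cost difference fixed at C, so that all variation comes from the denominator. A difference of x disease-free patients between the arms gives a ratio of 370C/x per additional disease-free patient. Leaving out the 4.9% of trials with x = 0, the middle 50% of ratios runs from about −62C to +62C and the central 95% from −370C to +370C. The latter limits correspond to a difference of a single patient. No cost figures are needed for this result.

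**Step 5: interval for the ratio.** A 95% Fieller interval is bounded only when the denominator differs significantly from zero, that is, when |difference|/SE > 1.96.

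**Step 6: sensitivity to the true difference** (normal approximation).

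| True DFS difference, laparoscopic minus open | P(denominator > 0) | P(Fieller interval bounded) |
|---|---|---|
| −2 points | 19% | 14% |
| −1 point | 33% | 7% |
| 0 | 50% | 5% |
| +1 point | 68% | 7.5% |
| +2 points | 83% | 16% |
| +4 points | 98% | 52% |

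The sign becomes more reliable as the true difference grows, but the interval remains unbounded in most trials until the true gain is about 4 points.

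**The case against.** The strongest objection is that the ratio does not stand alone. The same sentence adds the QALY analysis, EQ-5D is scheduled at baseline and at every later assessment, and a health services questionnaire is scheduled at every post-surgery visit. This stands, and it limits the consequence. A reader might infer that the whole cost-effectiveness aim fails if the arms prove equivalent, or that the QALY ratio has the same flaw. The documents support neither inference. The Discussion expects better short-term well-being, so the QALY difference is not planned to be zero, and no QALY difference or standard error is given from which instability could be shown.

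Second, the sign is an even chance only at a true difference of zero. This also stands. The Introduction hopes for a lower recurrence rate, and a trial can succeed within its margin with a non-zero difference. Zero is nevertheless the implied planning value, and at +2 points the interval is still unbounded in about 84% of trials.

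Third, net benefit, thresholds and interval methods are commonly left to an analysis plan or a health-economics plan, and cost per unit of primary effect beside a cost-utility analysis is a conventional pairing. This stands as to missing detail, and none is alleged. The point concerns the measure that the article does fix, which does not suit a trial planned for equal DFS.

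Finally, a reader might object that DFS is not a functional outcome. That is loose wording with no analytic effect, since the sentence itself says the primary outcome is what is used.

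**Conclusion.** The point holds for the cost-per-DFS ratio and no further. Under the trial's own planning assumption of equal DFS, with 370 per arm at 90%, the denominator has a standard error of 2.2 points around zero, is as likely to be negative as positive, and is exactly zero in about 5% of trials. A 95% interval for the ratio is bounded in about 5% of trials, rising to about 16% at a true gain of 2 points.

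These figures assume binomial variance and complete follow-up to 4.5 years; censoring or dropout would make the ratio less stable. They do not depend on alpha, on power, or on which of the article's differing margins is meant.

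The primary analysis is untouched, and the cost-effectiveness aim remains answerable through the QALY analysis. This is a minor but worthwhile correction.

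**What to change.** Remove the cost-per-DFS ratio as a stated measure. Report the difference in mean cost and the difference in EQ-5D QALYs between arms, each with a 95% interval. Combine them as incremental net monetary benefit (threshold × QALY difference − cost difference) at pre-stated thresholds, with a bootstrap 95% interval. Net benefit is a difference, so it has a finite estimate and interval even when the health gain is near zero.

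The change is to wording and analysis only; EQ-5D and the health services questionnaire are already in the assessment schedule. The price is that one or more thresholds must be chosen and justified in advance, and that no cost-per-DFS figure will be available for comparison with other studies.
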